#### *5.5.1 Stretching and strengthening of the periscapular muscles*

Both groups will perform stretching and strengthening protocol proposed by Camargo et al (53). Stretching of the upper trapezius will be performed actively with the individual performing lateral flexion of the neck, in both sides; the pectoralis minor stretching will be performed with the individual facing two walls

with a 90° angle between them, with shoulder elevation in the scapular plane of 90° and elbow flexion at 90°, and the individual will be instructed to project the body forward as far as they can. Posterior shoulder stretching will be performed with the horizontal adduction of the shoulder, with the individuals supported on the wall in order to avoid stabilizing the scapula (54). 3 sets of 30 seconds will be performed for each stretch, with an interval of 30 seconds between repetitions (53).

To strengthen the serratus anterior, the scapula protraction exercise will be performed in supine with shoulder flexed at 90°; and to strengthen the lower trapezius muscle, shoulder extension exercises will be performed with the elbow extended and the individual in prone position. For strengthening, 3 sets of 10 repetitions will be performed with 1 minute rest. Exercise resistance will be offered by means of elastic bands with progression determined by changing the colors of the bands, according to the individual's perception, so that as soon as the exercise is performed without difficulty and fatigue, the elastic band will be replaced by one with greater resistance (53).

#### *5.5.2 Isometric Exercise Group*

Isometric exercises for RC muscles will consist of 3 repetitions of 32 seconds at an intensity of 70% of the maximum isometric strength for each exercise, according to the protocol adapted from Rio et al. (27,28), and with an interval between repetitions of 80 seconds (26). The evaluation of maximum strength as well as the performance of the exercises will be performed with a manual dynamometer coupled to a rigid bulkhead and attached to a fixed wooden column. The dynamometer has a function which allows real-time monitoring of the developed force, allowing a visual feedback that will show the individuals the maintenance of the determined load during the exercise.

The determination of maximum isometric strength for the supraspinatus and internal and external rotator muscles will be performed during the shoulder strength assessment described above. The positioning of the individuals to perform the isometric exercises for these muscle groups will be the same as in the evaluation. Elevation of the shoulder in the plane of the scapula at 90° was adopted because it presents a lower risk of compression of the supraspinatus in the coracoacromial arch and, consequently, generates less pain and additional

injuries than exercises at lower arm elevation angles (55). The elevation movement should be performed with the thumb facing upwards, as the supraspinatus muscle is more selective compared to the middle and posterior deltoids (56).

In order to carry out the exercises, the individuals will be instructed to push the dynamometer in the direction of the desired movement and follow the sound feedback of the equipment, pre-adjusted to 70% of the maximum force, and the researcher responsible for the training will give verbal feedback so that the individuals avoid change of positioning or compensation and to avoid excessive contraction of the upper trapezius during the supraspinatus exercise.

### *5.5.3 Isotonic Exercise Group*

Isotonic exercises for strengthening RC muscles in a concentric and eccentric way will be performed using dumbbells. The exercises will consist of 3 sets of 8 repetitions of each exercise at an intensity of 8 RM, with load reassessment in the third and fifth week of intervention, according to the protocol adapted from Kongsgaard et al. (24). The rest interval between sets of exercises will be 80 seconds (28).

The external rotation exercise will be performed in side lying on the contralateral shoulder, with shoulder at 0° of abduction and flexion and elbow flexion at 90° with a towel between the lower part of the arm and the trunk of the individuals. For internal rotation, the patient will be positioned in side lying on the limb to be strengthened with the shoulder at 0° of abduction and flexion and elbow flexion at 90° (22). The participants will be instructed to perform the concentric and eccentric exercises at a pace of 3 seconds for each contraction mode, which will be controlled by a metronome that will also serve as feedback to the participants (57).

To strengthen the supraspinatus, an arm elevation will be performed in scapular plane with a neutral wrist and thumb upwards, in a range of 60 to 90°, since in this range there is less risk of compression of the supraspinatus in the coracoacromial arch and, consequently, less risk of increasing pain and generating additional injuries than at lower arm elevation angles (55).

## 5.6 Ethical aspects

The study will be submitted to evaluation by the Ethics Committee for Research on Human Beings and will respect the guidelines and norms contained in Resolution 466/12 of the National Health Council, which concerns ethics in carrying out research with human beings, advocating discretion and respect for research participants throughout the data collection, and must guarantee their duties and rights. All users must voluntarily assent their participation, which will be made explicit by signing two copies of the Informed Consent Form and the Authorization Term for Image Use.

The risks inherent to this research are minimal and the presence of some painful discomfort may occur during the evaluation and intervention procedures. Thus, individuals will have the right to withdraw from the research at any time they wish and the responsible researcher will have the duty to solve all their doubts and guarantee the privacy and confidentiality of the research participant, always having to be transparent about the procedures that will be carried out. If there is any physical damage, assistance and physiotherapy will be provided to the volunteer at the school clinics in the respective areas.

As for the promoted benefits, the participant will be contributing to the scientific community, as he will encourage an evidence-based physiotherapeutic practice. In addition, they will receive a complete and detailed assessment of the kinetic and functional conditions of their shoulder.

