## **2 Rationale**

RC tendon disease, both symptomatic and asymptomatic, have a high

prevalence in the general population, reaching up to 30% (31). This dysfunction is related to biomechanical factors, life habits and genetic predisposition, and influenced by age and overload to the tendons (5,32). The great clinical relevance of this condition is due to the fact that there is a high risk of progression of the tendinopathy to partial or total rupture of the tendons, causing symptoms of pain, weakness (32), and important functional limitations (33).

Conservative treatment, based on physiotherapeutic intervention, is indicated for treating RC tendinopathies and ruptures (32), especially resistance training which progressively imposes load on the tendon, in order to help in its repair by altering its metabolism and mechanical and structural properties (6). Among the various forms of resistance, eccentric and concentric exercises have been shown to be effective in improving overall shoulder function (22), and few studies (4,30) have been developed evaluating the effects of isometric exercise on RC tendinopathy.

However, isometric exercise has emerged as an important approach to improve pain in tendinopathies (27–29) and, when compared to isotonic exercise, it has been shown to be superior in terms of pain, strength, function in general, as well as in the reduction of cortical inhibition in the treatment of patellar tendinopathy (27). Thus, the rationale is the clinical relevance of evaluating the effects of isometric exercise applied to RC tendinopathy on pain, function and neuromuscular control involved in the shoulder complex. In this context, this study can help in clinical decision-making regarding the best approach to be considered in the treatment of RC tendinopathy.

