#### 5.4 Evaluation procedures

All included individuals will undergo the following assessments: a) pain and general function of the shoulder complex; b) electromyographic activity of the shoulder complex musculature during maximal isometric contractions; and c) electromyographic activity of the shoulder complex muscles during arm elevation in the scapula plane.

This evaluation sequence will be carried out in three moments: 1) initial evaluation, immediately before the first intervention session; 2) immediately after the first exercise session; and 3) after six weeks of intervention. All evaluations will be carried out by an evaluator who will not know which intervention group the individuals belong to (blind evaluator), with the interventions applied by two other trained researchers.

One week before the initial assessment, individuals will be randomly allocated using the online randomization tool for randomized clinical trials, available on the website ([www.randomization.com](http://www.randomization.com)). To guarantee the confidentiality of the allocation of individuals, this will be carried out by one of those responsible for applying the intervention, who will be the only one to know which group the individuals belong to. After determining the group, individuals will be introduced to the evaluation process and equipment, and will undergo a test to determine the elastic band to be used during periscapular muscle strengthening exercises. In addition, individuals allocated to the isometric or isotonic exercise group will perform the initial load determination test for each of the exercises. The sequences of the study procedures are described in Figure 1.

[figure not shown]

**Figure 1.** Study's flowchart.

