Active surface electrodes composed of an Ag/AgCl system associated with a conductive gel, simple differential, of bipolar configuration with dimensions of 4 cm X 2.2 cm of adhesive area and 1 cm of conductive area separated by 2 cm between electrode will be used (Miotec®, Brazil). A reference electrode of monopolar configuration will also be used, composed of an Ag/AgCl system associated with a conductive gel, with a diameter of 3.8 cm of adhesive area and 1 cm of conductive area (Miotec®, USA).

The positioning of sensors for the evaluation of lower trapezius, serratus anterior, middle deltoid and infraspinatus will follow the procedure described in

Michener et al. (46). A reference electrode will be attached to the ulnar styloid process on the contralateral side (48). Before placing the electrodes, the skin of the assessed regions will be shaved and cleaned with alcohol. The electromyographic activity will be evaluated only in the muscles of the symptomatic side, and after the tests, the individuals will be questioned about their pain, using the Numerical Pain Rating Scale (0-10, with 0 being no pain and 10 being the worst possible pain). (49).

To evaluate the amplitude of the electromyographic signal of each muscle and subsequently measure the muscle activation ratio between muscle pairs, the raw data will be filtered at a bandpass frequency of 20-450 Hz, rectified and smoothed using an algorithm of root mean square (RMS) with a 50-millisecond moving window, using Matlab software.

The ratio of muscle activation between the following pairs will be evaluated: 1) infraspinatus and middle deltoid; 2) infraspinatus and lower trapezius; and 3) lower trapezius and serratus anterior. These muscle pairs were selected since individuals with RC dysfunction have increased compensatory activity of the middle portion of the deltoid (14–16) and incoordination between the lower trapezius and serratus anterior and between the upper and lower portions of the trapezius (13).

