### 5.5 Intervention Protocol

Individuals from each group will perform an exercise session according to their group (isometric and isotonic) on the day of baseline assessment in order to verify the immediate effects of exercises. Then, they will participate in a six-week intervention, twice a week, in order to verify the effects of a strengthening program directed at the RC. Exercises will be performed on both limbs.

Individuals from all groups will undergo a protocol for stretching and strengthening the periscapular musculature following the protocol used by Camargo et al (53), which consists of stretching the upper trapezius and pectoralis minor muscles and the posterior portion of the shoulder, and strengthening the serratus anterior and lower trapezius muscles.

The evaluation to determine the initial loads of the exercises will be carried out one week before the baseline evaluation and beginning of the interventions. At that moment, participants will also familiarize themselves with each exercise with light resistance and will be guided by the evaluator to perform the technique correctly. In order to adjust and progress the exercise load over the six weeks of intervention, the assessments will be repeated in the third and fifth weeks of intervention, as shown in Figure 2 with the flowchart of the intervention procedures and progression of each group.

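### Painful discomfort is the one specific risk named, but the readable plan records no flares, injuries or reasons for stopping between session 1 and week 6, and does not separate stopping exercise from leaving the study

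*Combined protocol and SAP*

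**What the plan says.** Section 5.6 names a single specific risk: "The risks inherent to this research are minimal and the presence of some painful discomfort may occur during the evaluation and intervention procedures". The next sentence turns to withdrawal: "Thus, individuals will have the right to withdraw from the research at any time they wish". A further provision covers injury: "If there is any physical damage, assistance and physiotherapy will be provided to the volunteer at the school clinics".

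Section 5.4 sets three evaluations. The first comes immediately before the first session, and the others are "2) immediately after the first exercise session; and 3) after six weeks of intervention". Section 5.4.2 asks for the 0-10 pain rating (NPRS) after the EMG tests, so at those same times. Section 5.5 places one exercise session on the baseline day and then two sessions a week for six weeks. Work is at 70% of maximum isometric strength (5.5.2) or at 8 RM (5.5.3), and load is reassessed in weeks 3 and 5. The individual assessment form in the appendices is a screening form. Section 5.7 contains no safety analysis, analysis set or method for missing data. Section 5.2 makes pain on unloaded arm elevation the main outcome and allows for about 10% loss.

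**The concern.** The trial is meant to help clinicians choose between two loading programmes, and how each is tolerated from session to session is part of that choice. As written, a flare in week 2 that settles by week 6 leaves no trace. Nor does an injury in someone who does not return. Such data cannot be recovered afterwards.

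The second issue is the main outcome. The plan anticipates pain during the intervention, offers withdrawal from the research in the next sentence, and describes no intermediate status in which a participant stops the exercises but is still measured. A repeated-measures ANOVA in its usual form drops anyone without the six-week value. If participants in more pain left more often from one arm, that arm's completers would look better than the arm as randomised.

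**Working it through.** **1. What is recorded, and when**

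| Time | Pain or harm item in the readable text |
|---|---|
| Before session 1 | NPRS and questionnaires (5.4, 5.4.1, 5.4.2) |
| After session 1 | the same |
| Six weeks, twice weekly: 6 × 2 = 12 sessions | none |
| Weeks 3 and 5 | load reassessment only (5.5) |
| Six weeks | NPRS and questionnaires |

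**2. The plan's own sample size.** Inputs from 5.2: difference 2.05, SD 2.30, power 80%, α 0.05 (two-sided assumed).
- Normal approximation: n = 2 × 2.30² × (1.960 + 0.842)² / 2.05² = 19.76, so 20 per group.
- Exact two-sample t test: 20 per group gives 78.4% and 21 gives 80.5%. The stated 21 reproduces.
- Loss allowance: 21 × 1.1 = 23.1, or 21 / 0.9 = 23.3. Either is consistent with 23. With 23 per group, power is 84.0%.
- Losing 2 of 23 (8.7%) at random from each arm leaves 21 and 80.5%. The allowance covers loss unrelated to pain.

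**3. Bias if loss is related to pain in one arm only.** Suppose k of 23 leave and would have scored e points above the completers' mean m. The full-arm mean is m + k × e / 23, so the completers understate it by k × e / 23. The documents give neither k nor e; both are assumptions.

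| k | e | Bias (NPRS points) | Share of 2.05 |
|---|---|---|---|
| 1 | 3 | 3/23 = 0.13 | 6% |
| 2 | 4 | 8/23 = 0.35 | 17% |
| 3 | 4 | 12/23 = 0.52 | 25% |

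**4. Effect on power for the middle row.** One arm keeps 23 and the other 21. SE = 2.30 × √(1/21 + 1/23) = 0.694, with 42 df and critical t 2.018.
- No bias: 2.05 / 0.694 = 2.95, power 82.3%.
- Loss in the arm with more pain: 2.05 − 0.35 = 1.70; 1.70 / 0.694 = 2.45, power 66.7%.

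**5. How extreme that is.** In simulated normal samples of 23 with SD 2.30, the highest two values exceed the rest by 4.3 points on average, so e = 4 with k = 2 is close to losing exactly the two worst. Removing those two gives a bias of 0.37. With no true difference, type I error is about 9.7%. With a true difference of 2.05, power is about 70%; it exceeds 66.7% because removing extremes also shrinks the spread, whereas step 4 holds the SD at 2.30. In a milder model, where leaving correlates 0.3 to 0.8 with pain at 8.7% loss in one arm, the bias is 0.12 to 0.32. Similar loss in both arms largely cancels in the difference.

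**The case against.** Four stronger readings are tempting, and the documents do not support them.

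- **Withdrawal is the only response to harm.** Section 5.6 also promises assistance and physiotherapy for physical damage. What remains true is that nothing short of withdrawal is described for pain that is not physical damage.
- **Harms are invisible.** NPRS and the three Penn Shoulder Score pain items are taken in both arms at all three evaluations, and the WORC asks about the last week. Persisting pain would show in those who return. Only transient flares, and harms in those who leave, are missed.
- **The untreated-for shoulder has no pain score.** Section 5.5 says "Exercises will be performed on both limbs", and 5.4.2 says "The electromyographic activity will be evaluated only in the muscles of the symptomatic side", but the latter restricts EMG, not pain. The abstract has pain rated in the functional tests, and 5.4.3 performs them on each side.
- **Section 2 contradicts the minimal-risk statement.** Section 2 says "there is a high risk of progression of the tendinopathy to partial or total rupture of the tendons". That describes the disease, whereas 5.6 describes the risk of taking part. The two can both hold.

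It can also fairly be said that the right to withdraw is a general ethics clause. It does not direct people in pain to leave, and it does not cancel the six-week visit for those who stop exercising. Section 5.2 gives no reason for its 10% loss and no difference between arms. Outcome-related loss is therefore a possibility, not a finding, and loss after session 1 cannot touch the immediate comparison.

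Figures 1 and 2 are not shown and the consent pages were removed, so a recording step there cannot be excluded. None of this supplies a session-level record in the readable text.

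**Conclusion.** The point holds in a limited form. Followed as readable, the plan cannot report session-level pain, injury or reasons for stopping by arm, and it leaves open whether someone who stops exercising is still measured at six weeks. That gap follows from the text and needs no assumption about why people leave.

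The bias is conditional. It needs loss related to pain and unequal between arms. At the planned loss in one arm, a plausible range is 0.12 to 0.32 NPRS points, with about 0.35 near the worst case (17% of 2.05). Its direction depends on the arm: loss from the arm with more pain hides a true difference, while loss from the other arm exaggerates it. The sample size itself is not in question. This is a cheap improvement, not a fatal flaw.

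**What to change.** - **Session log (5.5).** At every session the treating researchers, not the blinded evaluator, record pain, any new injury or unplanned care, and the reason and date of any stop. Report these by arm, and add that summary to 5.7.
- **Two kinds of stopping (5.6).** Distinguish stopping the exercises from leaving the research. Participants who stop the exercises are, if they agree, still asked to attend the six-week evaluation, and are kept in the analysis in their allocated group.
- **If Figure 1, Figure 2 or the consent form already contains such a step,** state it in the text.

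This concerns recording and follow-up only; it sets no dose and no clinical stopping rule.

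Cost: 46 participants × 13 sessions (1 + 12) = 598 brief entries by staff already delivering the sessions. Scoring pain before and after each session doubles the ratings to 1,196, and doing so for both shoulders makes 2,392, so the simpler form may suffice. There is also the effort of bringing back those who stop. The log has limited precision: no events in 23 participants would still leave a one-sided 95% upper limit of 1 − 0.05^(1/23) = 12.2%.

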## 5.7 Statistical analysis

Data will be analyzed statistically in a descriptive and inferential way. Mean and standard deviation will be calculated for all demographics and dependent variables. Regarding inferential analyses, initially, the Shapiro-Wilk Normality Test will be used to classify the distribution of each variable.

In order to perform the comparison between the two groups (isometric and isotonic) and between the evaluations, for each dependent variable, we will apply two-way ANOVA with repeated measures when the data are considered parametric and Friedman when the data are non-parametric.

When necessary, post hoc Tukey or Duncan tests will be applied, respectively. All tests will be performed using the Statistical Package for Social Sciences – SPSS, version 20.0 software, and the significance level adopted will be  $\alpha \leq 0,05$ .

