## 5.2 Sample

Forty-six individuals with a clinical diagnosis of unilateral tendinopathy of the supraspinatus and/or infraspinatus tendon by means of ultrasonography (US) or nuclear magnetic resonance (NMR) exams, between 18 and 60 years of age, of both sexes will participate in this study. They will be randomly divided and allocated into two exercise groups, with 23 individuals each: 1) isometric group, which will undergo an isometric resistance training protocol for the RC musculature associated with a stretching and strengthening protocol focused on the periscapular musculature; and 2) isotonic group, which will undergo an isotonic resistance training protocol for the RC musculature associated with a stretching and strengthening protocol focused on the periscapular musculature.

Sampling will be non-probabilistic type of consecutive cases, where individuals will be recruited from a waiting list for physiotherapeutic care in the Physical Therapy Department of UFRN and through dissemination carried out at UFRN, in the city of Natal-RN and social media through posters. The sample size was determined considering the main outcome variable, pain with arm elevation without load, considering a difference between means of 2.05 and standard deviation of 2.30 in the numerical pain rating scale (NPRS) (34). Adopting a 80% Power and  $\alpha = 0.05$ , at least 21 individuals per group will be required. Considering possible sample losses of approximately 10%, the sample should be at least 23 individuals per group.

This project will be sent to the Ethics and Research Committee of UFRN (CEP/UFRN), through the registration in Plataforma Brasil, and will only start its activities after approval. All volunteers will receive a verbal and written explanation of the objectives and methodology of the study, as well as its risks and benefits; and those who agree to participate must sign an informed consent form, in accordance with Resolution 466/12 of the National Health Council, confirming their participation in the study. The project will be submitted to the Brazilian Registry of Clinical Trials (<http://www.ensaiosclinicos.gov.br/>) before

starting to recruit individuals.

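### The sample size rests on a single two-group difference in pain, but the planned test is a three-visit repeated-measures ANOVA that includes baseline, so the stated 80% power is not shown to carry over

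*Combined protocol and SAP*

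**What the plan says.** Section 5.2 names the outcome used for sizing: "The sample size was determined considering the main outcome variable, pain with arm elevation without load". The inputs are given as "considering a difference between means of 2.05 and standard deviation of 2.30 in the numerical pain rating scale (NPRS", followed by "Adopting a 80% Power" and a 0.05 significance level. The result is that "at least 21 individuals per group will be required", and then: "Considering possible sample losses of approximately 10%, the sample should be at least 23 individuals per group". The section does not say at which visit the difference applies, whether 2.30 is the SD of raw scores or of change, or which test is meant.

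Section 5.4 sets three evaluations. The first is before the first session, and the others are "2) immediately after the first exercise session; and 3) after six weeks of intervention".

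Section 5.7 begins its inferential plan with "In order to perform the comparison between the two groups (isometric and isotonic) and between the evaluations, for each dependent variable" and specifies a two-way repeated-measures ANOVA, or Friedman when data are judged non-parametric, with Tukey or Duncan post hoc tests if needed, in SPSS 20. It names no baseline covariate, primary contrast, primary time point, confidence interval, sphericity correction or missing-data rule.

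Section 4 states the hypothesis as superiority of isometric exercise over isotonic exercise at two times: immediately and after six weeks.

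**The concern.** The hypothesis is about two between-group contrasts, and neither is a standard output of the planned ANOVA.

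- The group main effect averages over all three visits, including baseline, where randomisation makes the expected difference zero.
- The interaction is a joint test on 2 degrees of freedom. It does not say at which visit the groups differ, or by how much.
- The time effect is a within-person change. Both groups also receive the same stretching and periscapular programme (section 5.5.1), so this change cannot be attributed to either type of rotator cuff exercise.

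Two things are at stake. The power in section 5.2 may not be the power of the test that is run. And with no named contrast, the result to be emphasised can be chosen after the data are seen. Missing data add a smaller issue: a classical repeated-measures ANOVA ordinarily needs all three visits, so someone lost before week 6 would also leave the immediate comparison, although their data for it had already been collected.

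**Working it through.** **Inputs from section 5.2:** difference D = 2.05, SD = 2.30, alpha 0.05 (taken as two-sided), 21 completers per group. **Assumed, because the documents do not give it:** within-person correlation rho from 0.2 to 0.7, equal between all pairs of visits, with 2.30 as the raw-score SD.

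**1. The plan's own figure.** The standardised difference is 2.05/2.30 = 0.891. For a two-sided two-sample t-test the noncentral t distribution gives power 78.4% at 20 per group and 80.5% at 21. The stated 21 reproduces. It would reproduce equally as a two-sample test on change scores with an SD of change of 2.30.

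**2. Interaction.** The noncentrality is (n/2) × Σ(d_j − d̄)² / [SD²(1 − rho)], referred to F with 2 and 80 df. The d_j are the group differences at baseline, immediately and at six weeks.

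- Full effect at six weeks only (0, 0, D) or at both visits (0, D, D): Σ = (2/3) × 2.05² = 2.802, so the noncentrality is 10.5 × 2.802 / [5.29(1 − rho)] = 5.56/(1 − rho).
- Half the effect immediately, all of it at six weeks (0, D/2, D): Σ = 2.05²/2 = 2.101, so the noncentrality is 4.17/(1 − rho).

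**3. Group main effect.** The difference in person means is D/3 = 0.683 (six weeks only) or 2D/3 = 1.367 (both visits). The SD of a person mean is 2.30 × √[(1 + 2rho)/3].

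**4. Six-week contrast adjusted for baseline.** Difference 2.05, residual SD 2.30 × √(1 − rho²).

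Power (%) with 21 per group:

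| rho | Interaction, full effect | Interaction, half immediately | Main effect, week 6 only | Main effect, both visits | Baseline-adjusted week 6 |
|---|---|---|---|---|---|
| 0.2 | 63.5 | 50.5 | 28.0 | 78.5 | 82.0 |
| 0.3 | 69.7 | 56.4 | 25.1 | 73.0 | 83.9 |
| 0.4 | 76.7 | 63.5 | 22.8 | 67.9 | 86.7 |
| 0.5 | 84.3 | 71.9 | 21.0 | 63.4 | 90.2 |
| 0.6 | 91.6 | 81.7 | 19.5 | 59.3 | 94.1 |
| 0.7 | 97.3 | 91.6 | 18.3 | 55.6 | 97.6 |

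The interaction reaches 80% at rho of about 0.44 (full effect) or 0.58 (half immediately).

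**5. If 2.30 is the SD of change.** Then SD²(1 − rho) = 2.30²/2 = 2.645. The noncentrality is 11.12 or 8.34, and interaction power is 84% or 72%, whatever rho is.

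**6. Unequal correlations.** Two visits fall on one day and the third about six weeks later. With 0.7 between the same-day visits and 0.3 with week 6 (both assumed; 20,000 simulations), interaction power is 73% for an effect at six weeks only, 83% at both visits and 63% with half immediately. With a Greenhouse-Geisser correction these become 70%, 79% and 59%.

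**7. Losses.** A 10% loss from 23 leaves 23 × 0.9 = 20.7 per group, with t-test power 79.9%. If later dropouts were removed from the immediate comparison, its standard error would rise by √(23/20.7) = 1.054, about 5% relative to keeping all 23.

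**The case against.** The strongest reply is that repeated-measures ANOVA is a legitimate analysis of randomised data and that the mismatch can work in the plan's favour. That stands in part. At rho of 0.5 or more the full-effect interaction has more power than the t-test behind section 5.2. If 2.30 is an SD of change, the sizing matches a one-degree-of-freedom comparison of change between groups. The group main effect is nowhere declared decisive. Section 5.7 also allows post hoc tests, though it does not say that they compare groups at a given visit.

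Four stronger readings are tempting, and the documents do not support them.

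- A reader might infer that participants who miss a visit will be dropped. No such rule is written. Missing-data handling is simply not stated, and deletion is only how the named method is usually run.
- A reader might infer that dropout takes power below target. The step from 21 to 23 already budgets for a loss of about 10%. What remains is possible bias and avoidable loss of immediate-effect data.
- A reader might infer an inflated type I error. Simulation gives 7.0% to 7.5% for the uncorrected interaction, but only with an assumed same-day correlation of 0.9 against 0.3 to 0.4 with week 6. The documents supply none of these values and do not say that a correction would be left out.
- A reader might take six weeks as the primary time. Sections 3.2 and 4 name both times and rank neither.

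**Conclusion.** The point holds as a gap between sizing and analysis. The 21 per group is right for a two-sample comparison, but the documents give no correlation, contrast or time point that would transfer the 80% to the planned ANOVA. Whether the interaction meets 80% depends on an unstated correlation and on how the effect is spread over the visits. The main effect does not meet it in any pattern tried.

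This does not show that the trial is underpowered. Under the same inputs, 21 per group is enough for a six-week contrast adjusted for baseline at every correlation considered. These figures rest on the assumed correlations, on 2.05 being a between-group difference (inferred because the two-sample formula reproduces 21) and, except in step 5, on 2.30 being a raw-score SD. The change should be made because it answers the trial's own question with more power at no cost in patients. It is not a reason to hold the trial back.

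**What to change.** In section 5.7, replace the ANOVA with a linear mixed model (SPSS MIXED). The responses are the immediate and six-week values. The fixed effects are group, time, group-by-time and the baseline value, with unstructured covariance. Include all randomised participants, as allocated, who have any post-baseline value. This also settles how a missed visit is handled.

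Report the between-group difference with a 95% CI at each of the two times, and base any superiority claim on these and not on within-group change. Use the same between-group contrasts for variables now sent to the Friedman test, which ranks visits within a person and does not compare the two groups.

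Before analysis, the sponsor should name which time point is primary. In section 5.2 it should state the visit to which 2.05 applies, whether 2.30 is an SD of raw scores or of change, and the correlation assumed. If the immediate time point is chosen, 2.05 has to be justified for that visit.

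The cost is revised wording and slightly more analysis work. Baseline is already collected, and no further patients or visits are needed.
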